## Analysis plan

Basic descriptors will be used to summarise the characteristics of the overall trial population, each arm, and participants who decline any element of the trial. The characteristics of people who decline participation will be compared with the trial population using means, confidence intervals, chi-squared and unpaired T-tests. If possible, multivariable regression modelling will be undertaken to explore which factors were associated with non-acceptance of OK432/BCG.

Feasibility outcomes, including recruitment, randomisation and trial completion rates, will be described for the overall trial and for each arm. Secondary outcomes will be summarised for each arm based on randomisation, i.e. intention to treat. Per protocol and compliance averaged causal effects (CACE) analysis will be undertaken as secondary analyses for clinical efficacy outcomes.

Time to event data will be analysed using the Kaplan-Meier method. Cox proportional hazards modelling will be used to calculate hazard ratios for death and pleurodesis. Univariable modelling will be used, followed by multi-variable methods to control for potential confounders. The time-independent confounders to be considered are age, sex, performance status, tumour histology and whether chemotherapy was received. Time-dependent confounders that will be adjusted for are the time between diagnosis with MPM and baseline assessment, and length of time the IPC was in situ. The main analysis will include all patients. A priori sub-group analyses will stratify patients according to time since diagnosis (≥8 weeks versus <8 weeks) and whether chemotherapy was received.

Pleurodesis rates will be calculated for the whole population, and in the sub-group of patients who’s IPC had been in situ for less than 6 weeks at baseline assessment.

Outcomes with repeat measurements, e.g. PROMS and biomarker responses, will be analysed using regression modelling with adjustment for baseline values. Survival rates will be compared with national survival data, and survival rates from previous clinical trials of new treatments in MPM. Progression-free survival rates will be compared to validated values for acceptable clinical activity of new oncological agents in MPM.^99^

Statistical analysis will be undertaken using Stata (StataCorp LP) version 14, with support from YTU.

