## Sample size & recruitment targets

The target sample size is 12 participants, of whom 8 will be randomly selected to be offered OK432 or BCG and 4 will continue in ASSESS-meso as controls. This sample size is based on previous feasibility studies in mesothelioma.

It is anticipated that the majority of participants who are offered bacterial immunotherapy will consent to receive it, as the burden of treatment is low (a single dose on one occasion), the treatment intervention is well established in other clinical scenarios and trial follow up assessments are the same as they would be within ASSESS-meso. Non-acceptance of bacterial immunotherapy will be collected as part of the feasibility outcomes for the trial, and qualitative interviews will explore these participants’ reasons for non-acceptance of bacterial immunotherapy.

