## Feasibility assessments

The primary outcome for the trial is feasibility. This will be based the following feasibility targets:

- Recruitment rates to time & target >66% at end of the trial
- Attrition rate of <20% (nb this relates solely to attrition due to loss to follow up or participant withdrawal, it does not include attrition due to participant death)
- Data completeness rates >90%

In addition, data will be collected on specific elements of the TwiC methodology to explore the acceptability of the trial design to participants. This will include determining how many participants in the control arm were aware that the intervention arm existed, and that they had been randomised to be controls. Information will also be collected on the number of participants who were randomly selected to receive either OK432 or BCG, but declined to do so. These participants will continue to be followed up in accordance with the TILT protocol. In order to determine whether participants who decline bacterial immunotherapy differ in any way to other study participants, their baseline characteristics and clinical outcomes will be compared with the control arm and with participants who received immunotherapy, as described in Section 13.

Data from ASSESS-meso will also be used to explore the characteristics and outcomes of patients who consented to join ASSESS-meso but declined to be considered for future trials.

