# STATISTICAL ANALYSIS

## Primary outcome measure

The primary outcome measure is feasibility, which will be assessed based on the following criteria:

- Recruitment rates to TILT
- Feasibility of identifying and randomising 12 eligible participants
- Acceptance rates for intra-pleural OK432/BCG following random selection
- Collection of data on participants who declined to receive OK432/BCG when offered it
- Collection of data on participants within ASSESS-meso who declined to be considered for future trials
- Number of participants in the control arm who were aware of the intervention arm
- Attrition rates and data completeness rates

In addition to feasibility data, qualitative interviews will be undertaken with participants and focus groups with their relatives/carers to explore the acceptability of trial processes. Analysis of the qualitative data is described in Section 10.3.

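### Whether people who decline OK432/BCG differ is to be settled by chi-squared and t-tests on a handful of decliners, where non-significance says little and single chi-squared p-values can be several times too small

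*Protocol*

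**What the plan says.** Section 9.2 (Feasibility assessments) gives the aim: "In order to determine whether participants who decline bacterial immunotherapy differ in any way to other study participants". The planned comparison takes in baseline data and outcomes, with controls and recipients as two separate comparators, and section 9.2 refers to section 13 for the method.

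Section 13.3 (Analysis plan) gives the method: "The characteristics of people who decline participation will be compared with the trial population using means, confidence intervals, chi-squared and unpaired T-tests". It names no exact test and no rule for sparse tables. The qualifier about what is possible attaches only to the multivariable model of non-acceptance in the sentence that follows.

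The numbers come from the section on sample size and recruitment targets: "The target sample size is 12 participants, of whom 8 will be randomly selected to be offered OK432 or BCG", with the expectation that "the majority of participants who are offered bacterial immunotherapy will consent to receive it". The size of the trial rests on precedent: "This sample size is based on previous feasibility studies in mesothelioma". No significance level, power or difference of interest is given for the decliner comparison.

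Section 13.1 also lists a second group of people who decline: "Collection of data on participants within ASSESS-meso who declined to be considered for future trials". Their number is not stated, and they are not among the 8 people offered treatment.

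**The concern.** The aim in section 9.2 is worded as a yes/no determination, and section 13.3 answers it with significance tests. With so few decliners, a non-significant t-test is the likely result whether or not they differ, yet the wording of the aim invites reading it as showing no difference. In the other direction, the chi-squared approximation is poor when expected counts are this small, so an isolated small p-value could be taken as a signal when the exact test gives none.

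This matters because the trial is meant to inform a full-scale trial within a cohort. In that design refusal comes after randomisation, and section 13.3 analyses secondary outcomes by randomised arm. Selective refusal would therefore dilute the estimated effect and narrow the population to which it applies. A misread test could mislead the next design on that question.

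**Working it through.** **Inputs from the protocol.** 12 randomised 1:1:1, so 12 × 2/3 = 8 are offered treatment and 4 are controls; this reproduces the stated 8. A majority of 8 accepting means at least 5 accept, so at most 8 − 5 = 3 decline if the expectation is met. With 3 decliners the comparators are 5 recipients and 4 controls, 9 others in all.

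**Assumptions, not in the protocol.** Two-sided 5% level; true differences of 0.5 to 2 SD; equal variances; Pearson chi-squared without continuity correction.

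**How firm is 3?** If each person accepts independently with probability q, the chance of 3 or fewer decliners among 8 is 59% at q = 0.6, 81% at 0.7, 94% at 0.8 and 99.5% at 0.9. So 3 is an expectation and not a limit.

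**T-test power.** The noncentrality is d × √(n1·n2/(n1+n2)) on n1+n2−2 degrees of freedom. For 3 v 9 this is d × √(27/12) = 1.5d on 10 df, critical value 2.228.

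| Groups | 0.5 SD | 0.8 SD | 1 SD | 1.5 SD | 2 SD |
|---|---|---|---|---|---|
| 3 v 9 (all others) | 10% | 19% | 27% | 53% | 77% |
| 3 v 5 (recipients) | 9% | 15% | 21% | 41% | 63% |
| 3 v 4 (controls) | 8% | 14% | 19% | 36% | 56% |
| 6 v 6 (best split of 12) | 12% | 24% | 35% | 65% | 88% |

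The miss rate is 100% minus these values. For 3 v 9 it is 90% at 0.5 SD, 73% at 1 SD and 23% at 2 SD. For 6 v 6 it is 65% at 1 SD. The low power for ordinary differences therefore does not hinge on there being exactly 3 decliners.

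**Width of the interval.** The 95% half-width for a difference in means is t × √(1/n1 + 1/n2) SD. For 3 v 9: 2.228 × √(1/3 + 1/9) = 2.228 × 0.667 = 1.49 SD. For 3 v 5: 2.447 × 0.730 = 1.79 SD. For 3 v 4: 2.571 × 0.764 = 1.96 SD.

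**Expected counts.** The smallest expected count in a 2x2 table is largest when the characteristic is evenly split: 3 × 6/12 = 1.5 for 3 v 9, 3 × 4/8 = 1.5 for 3 v 5, and 3 × 3/7 = 1.29 for 3 v 4.

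**Single p-values.** Chi-squared = N(ad − bc)²/(product of the four margins).

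| Decliners v others | Chi-squared | p | Fisher p |
|---|---|---|---|
| 1 of 2 v 0 of 10 | 12 × 10²/(2×10×1×11) = 5.45 | 0.020 | 0.167 |
| 3 of 3 v 1 of 5 | 8 × 12²/(3×5×4×4) = 4.80 | 0.028 | 0.143 |
| 3 of 3 v 3 of 9 | 12 × 18²/(3×9×6×6) = 4.00 | 0.046 | 0.182 |

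In each table the named test crosses 5% and the exact test does not. The ratio of the two p-values is about 4 to 9.

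**Overall false-positive rate.** Enumerating all tables at a nominal 5%, the worst rate over the possible true proportions is 6.5% for 3 v 9, 7.0% for 3 v 5, 7.8% for 3 v 4, 7.2% for 2 v 10, 7.4% for 1 v 11 and 5.5% for 2 v 6. At many true proportions it lies below 5%.

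**What an exact test changes.** At 3 v 9, Fisher's test keeps the error rate at or below 2.4% for the true rates tried (5% to 50%), but its power is 19% for 50% v 15% and 31% for 70% v 20%, against 21% and 37% for chi-squared. It repairs the p-value, not the power.

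**The case against.** The strongest reply is that little rests on this comparison. The feasibility criteria are recruitment, attrition and data completeness, and the section 13.1 item on decliners is met by collecting their data, not by a test result. No hypothesis or go/no-go rule is attached. The same sentence of section 13.3 already plans means and confidence intervals, which would display the uncertainty. Descriptive summaries, brief reasons for declining and interviews are planned as well. Choosing an exact test for sparse tables is often left to a statistical analysis plan, and low power is inherent in 12 participants. Most of this stands and limits the harm to misreading individual p-values. It does not remove the mismatch between an aim worded as a determination and the tests the protocol names for it.

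A reader might infer several stronger points that the protocol does not support:

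- **That there can be at most 3 decliners.** The text states only an anticipation.
- **That real differences are almost always missed.** This is fair up to about 0.8 SD, but 3 v 9 has 53% power at 1.5 SD and 77% at 2 SD.
- **That chi-squared is badly wrong overall.** Particular p-values are; the error rate is only mildly inflated.
- **That decliners are tested against a group containing them.** The phrase about the trial population in section 13.3 allows this reading, but section 9.2 names controls and recipients as separate comparators.
- **That the tests suit no one who declines.** The sentence in section 13.3 may also cover cohort members who declined future trials, and for a larger group the tests may be adequate.

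**Conclusion.** The concern holds in a limited form. For people who decline OK432/BCG after selection, the named tests do not fit the stated aim. With about 3 decliners, a non-significant t-test leaves differences of 1 SD largely unexcluded (73% missed at 3 v 9, 79% against 5 recipients, 81% against 4 controls), and single chi-squared p-values can be several times too small. The overall chi-squared false-positive rate does not exceed about 8%, and no feasibility decision depends on the result.

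This rests on 8 people offered treatment, a two-sided 5% level and uncorrected chi-squared. If instead the plain English summary's figures of 24 identified and 16 selected applied, up to 7 decliners would fit a majority accepting, and 7 v 17 would give 40% power at 0.8 SD and 57% at 1 SD. That is better, but still not enough to read non-significance as similarity.

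**What to change.** In section 13.3, for people who decline OK432/BCG after selection:

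- Replace the chi-squared and t-test p-values with an individual listing of each decliner's baseline characteristics, outcomes and reasons.
- Give differences with exact or t-based 95% confidence intervals against acceptors and against controls, as separate groups.
- Use Fisher's exact test if any categorical p-value is shown.
- State that a non-significant result will not be taken as evidence that decliners are similar.

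In section 9.2, change the aim from determining whether decliners differ to describing how they differ. Chi-squared and t-tests may stay for cohort members who declined future trials, where numbers allow, and section 13.3 should say which group each method serves.

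The cost is wording in two sections and the loss of p-values that carry little information. Data collection, sample size and conduct are unchanged. The power stays low; the change corrects the p-values and how they are read.

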## Study design

This is a multi-centre feasibility study for a single-blind, randomised, three-armed trial of intra-pleural bacterial immunotherapy in people with mesothelioma, based on the trial within a cohort design.

Patients with mesothelioma will be invited to participate in a longitudinal observational cohort study, consisting of pleural fluid monitoring, patient-reported outcome measurements, chest radiography (CXR) and blood tests (the ASSESS-meso study). Eligible patients will be identified from the cohort and randomly allocated to receive a single dose of either intra-pleural OK432 or intra-pleural BCG, or to remain in the cohort as a control. Identification of eligible participants will continue until 8 participants have been randomly selected to receive OK432 or BCG. Randomisation will be undertaken by a centralised, concealed computerised system with minimisation by tumour sub-type and WHO/ECOG performance status (PS). Participants selected to receive bacterial immunotherapy will receive it via an indwelling pleural catheter (IPC), on an unblinded basis. Participants who decline to receive OK432 or BCG following random selection will continue to undergo observational follow up, and their data will be collected as part of the feasibility outcomes.

Participants who are not selected to receive bacterial immunotherapy will continue longitudinal assessments as part of ASSESS-meso, blinded to the existence of the OK432 and BCG arms. This is consistent with real-life clinical care, wherein patients are told about treatments as and when they are going to receive them.

The primary outcome measure is feasibility. The trial will be deemed feasible if the following criteria are met:

- Recruitment rates to time & target >66%, i.e. 8 participants randomised in 12 month recruitment window, or 12 participants in 18 months.
- Attrition rate of <20% (nb this relates solely to attrition due to loss to follow up or participant withdrawal, it does not include attrition due to participant death)
- Data completeness rates >90%

In addition, data will be collected on specific elements of the TwiC methodology to explore the acceptability of the trial design to participants. These will include:

- Acceptance rates for intra-pleural OK432/BCG following random selection
- Number of control participants who were aware of the intervention arm
- Collection of data on participants who decline any element of the trial

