- Qualitative interviews with participants and their relatives to explore the acceptability of trial processes.

Secondary outcome measures will collect exploratory data on the clinical efficacy of OK432 and BCG. They will include:

- Tumour response, based on CT appearances at baseline and 3 months, assessed using modified RECIST^42^
- Overall survival (OS), defined as time between date of diagnosis with MPM to date of death, censored at the end of the trial (EoT)
- Progression-free survival rates (PFSR) at 3 months
- Patient-reported chest pain and breathlessness, measured on visual analogue scales (VAS)
- Patient-reported quality of life, measured using the EQ-5D-5L health questionnaire
- Pleurodesis rates, defined as pleural fluid drainage of less than 50ml on 3 consecutive occasions, with <25% opacification on CXR or <250ml pleural fluid on thoracic ultrasound scanning (TUS)
- Adverse events
- Biomarker response assessed using serial serum mesothelin levels.

Following completion of the trial, participants will return to follow up within ASSESS-meso cohort study until death or withdrawal from the cohort. This will yield additional data over time, and consequently a priori analyses are planned at 1 year and 2 years post-completion of TILT (i.e. following the final visit of the final participant) to evaluate overall survival, progression-free survival, adverse events and other long-term clinical outcomes.

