## Intervention visit

Participants who are randomised to bacterial immunotherapy will be invited to receive a single administration of OK432 or BCG, depending on which arm they are allocated to. The dose of OK432 is 10KE and the dose of BCG is 0.4-1.6x10^7^ CFU.. However, reduced dose options (5KE of OK432 and 0.2-0.8 x 10^7^ CFU of BCG) can be used (based on the discretion of the treating clinician) in older patients, those with higher performance status, people with multiple medical co-morbidities, or those at higher risk of experiencing or not coping with an adverse event. The immunotherapy agent will be delivered intra-pleurally via an indwelling pleural catheter within 14 days of random selection (i.e. days 0-14).

For the intervention visit, participants will attend hospital and undergo medical assessment to ensure they remain eligible and suitable to receive OK432/BCG. This will include complete drainage of the effusion, to ensure IPC patency, followed by a CXR to exclude trapped lung. If they remain eligible, up to 3mg/kg of 1% lignocaine (to a maximum of 250mg) will be instilled intra-pleurally followed by the appropriate agent, in adherence with the Trial Specific Protocol 4 (TSP 04). The IPC will then be disconnected and OK432/BCG left within the pleural cavity for 1 hour. After 1 hour, further drainage will be undertaken and the participant will be observed for another hour before returning home.

Following the intervention, patients will be advised to take regular prophylactic paracetamol and ibuprofen for the subsequent 3 days to reduce the risk of fevers, sweats and pain.

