## Secondary outcome measures

Secondary outcome measures will collect exploratory data on the clinical efficacy of OK432 and BCG. This data will be used to decide the primary outcome for the subsequent full-scale trial, and to estimate the variance of the chosen outcome for a sample-size calculation. Potential outcomes include:

- Tumour response, based on CT appearances at baseline and 12 weeks ^42^
- Overall survival (OS), defined as time between date of diagnosis with MPM to date of death, censored 12 weeks after the final trial visit of the final participant
- Progression-free survival rates (PFSR) at 12 weeks
- Patient-reported chest pain and breathlessness, measured on visual analogue scales (VAS)
- Patient-reported quality of life, measured using the EQ-5D-5L health questionnaire
- Pleurodesis rates, defined as pleural fluid drainage of less than 50ml on 3 consecutive occasions, with <25% opacification on CXR or <250ml pleural fluid on thoracic ultrasound scanning (TUS)
- Time to pleurodesis, calculated from baseline assessment to date of pleurodesis
- Biomarker response assessed using serial serum and pleural mesothelin levels

Participants will be followed up until death, or end of trial (EoT) 12 weeks after the final trial visit of the final participant, whichever is sooner.

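### Adverse events are a secondary outcome in section 2.3 but not in 13.2, so section 13 either counts undosed people in an agent's adverse event rate or gives no rule

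*Protocol*

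**What the plan says.** Section 2.3 (Study design) opens its list with "Secondary outcome measures will collect exploratory data on the clinical efficacy of OK432 and BCG. They will include" and names "Adverse events" as one item. It also plans analyses one and two years after completion, "to evaluate overall survival, progression-free survival, adverse events and other long-term clinical outcomes".

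Section 13.2 (Secondary outcome measures) begins with the same statement about exploratory efficacy data. It adds that the data will help choose the full trial's primary outcome and estimate its variance, and introduces its list with "Potential outcomes include". That list has eight items and adverse events are not among them.

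Section 13.3 (Analysis plan) sets the grouping: "Secondary outcomes will be summarised for each arm based on randomisation, i.e. intention to treat". Per-protocol and CACE "analysis will be undertaken as secondary analyses for clinical efficacy outcomes". It does not mention adverse events.

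The protocol provides for people who are allocated to an agent and not given it. Section 2.3 says "Participants who decline to receive OK432 or BCG following random selection will continue to undergo observational follow up". Under section 7.3 (Intervention visit), those who accept must still "undergo medical assessment to ensure they remain eligible and suitable to receive OK432/BCG".

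**The concern.** The two lists of secondary outcomes disagree about adverse events, and the analysis rule depends on which list is followed. Neither reading leaves safety with a suitable summary.

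In a trial within a cohort, people are allocated before they are asked about treatment, so non-receipt is an ordinary event in the active arms. Grouping by randomisation preserves the comparison for efficacy. For reactions to an agent it puts people who could not have reacted into the denominator. The protocol recognises that receipt matters, since it adds per-protocol and CACE analyses, but it confines these to efficacy.

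Section 12.2 notes that neither agent has been used in this setting in the UK, and section 2.2 says the results will inform whether one or both go into a full trial. Reaction rates that look lower than those among treated people, or a zero count that looks more reassuring than it is, would be a poor input to that choice. This matters most if acceptance differs between OK432 and BCG.

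**Working it through.** The plan states no figure to reproduce on this point. The check compares the two readings and then sizes the first.

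**The two lists.** Both 2.3 and 13.2 have eight items. Seven correspond: tumour response, overall survival, progression-free survival rate, symptom scores, EQ-5D-5L, pleurodesis rate and mesothelin. Adverse events appear only in 2.3; time to pleurodesis appears only in 13.2.

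- If 2.3 governs, adverse events are secondary outcomes, so 13.3 summarises them by randomised arm with no receipt-based analysis.
- If 13.2 governs, the 13.3 rule for secondary outcomes does not reach them, and section 13 says nothing else about them.

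These are alternatives; they cannot both operate.

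**Inputs for the size**

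- Arm size: 4. Section 6.6 gives 12 participants, 8 of them selected for an agent; the flowchart gives 4 per arm at 1:1:1.
- Undosed per arm: no rate is given. Section 6.6 expects only that most will accept. Assumed here: 0, 1 or 2.
- Reaction rate among the dosed: 23%, the OK432 fever figure in the background section on OK432, used only as an illustration.
- Reactions among the undosed: none. This matches section 12.4, which says unexposed cohort participants cannot have adverse reactions.

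**Formulas**

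- Expected rate by randomisation = 0.23 × dosed ÷ randomised.
- Exact one-sided 95% upper bound with zero events in n people = 1 − 0.05^(1/n).

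| Undosed of 4 | Dosed | Rate by randomisation | Rate by receipt | Zero-event bound by randomisation | Zero-event bound by receipt |
|---|---|---|---|---|---|
| 0 | 4 | 0.23 × 4/4 = 23.0% | 23.0% | 1 − 0.05^(1/4) = 52.7% | 52.7% |
| 1 | 3 | 0.23 × 3/4 = 17.3% | 23.0% | 52.7% | 1 − 0.05^(1/3) = 63.2% |
| 2 | 2 | 0.23 × 2/4 = 11.5% | 23.0% | 52.7% | 1 − 0.05^(1/2) = 77.6% |

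Each undosed person in an arm of 4 removes a quarter of the reaction rate.

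**Sensitivity to arm size.** The plain English summary speaks of 24 people with 16 selected, which would be 8 per arm. Then one undosed person gives 0.23 × 7/8 = 20.1% and two give 0.23 × 6/8 = 17.3%, against 23.0% by receipt. The two sample sizes need reconciling in any case.

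**The case against.** The strongest case against is that 13.2 is an efficacy list. It says it serves to choose a primary outcome for the full trial and to estimate that outcome's variance, and it is worded as open. On that reading the intention-to-treat sentence was written for efficacy, safety sits in sections 9.4 and 12, and what is left is an undefined safety population, which a protocol may leave to the SAP. The last step is right in itself: an unstated safety population alone would be no finding. But 2.3 places adverse events under the same efficacy lead-in, as a secondary outcome, and 13.3 fixes the grouping for secondary outcomes. The problem is a stated rule that does not suit safety data, not a missing detail.

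Section 9.2 promises to compare decliners' clinical outcomes with controls and with those treated, as described in section 13. That is close to the split needed. It does not name adverse events, however, and section 13.3 carries through only the comparison of characteristics.

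Several limits stand:

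- Causality grading (12.3), SAE and SUSAR reporting (12.5) and committee review (16.4) concern individual events and do not depend on the analysis grouping. A reader might infer that safety oversight is compromised; the protocol does not support that.
- A reader might infer that adverse events will go unanalysed. Section 2.3 plans adverse event analyses at one and two years, and the 13.2 list is not exhaustive.
- A reader might point to a reaction seen in every dosed person being shown as 75% (3/4) or 50% (2/4). The arithmetic is right, but it assumes both a non-dosing rate the protocol does not give and a reaction in everyone dosed.
- Acceptance is itself a feasibility outcome, so an attentive reader of the results could see how many were dosed. Nothing in the protocol says arm-level adverse event rates will by themselves decide which agent goes forward.

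**Conclusion.** The point holds in a limited form. Sections 2.3 and 13.2 disagree on whether adverse events are a secondary outcome. Under 2.3 the stated rule puts people who never received OK432 or BCG into that agent's safety denominator; under 13.2 section 13 gives no rule. Either way the text needs correcting.

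The effect is confined to arm-level summary rates. Its size rests on an assumed 0 to 2 undosed people in an arm of 4: nothing if everyone is dosed, and with two undosed the reaction rate is halved. The 23% is borrowed from the protocol's OK432 fever reports and no such figure is given for BCG, so only the proportional shrinkage carries over to BCG. The dilution applies to reactions caused by the agent. For all-cause adverse events, undosed people bring their own background events and the direction is not fixed.

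**What to change.** 1. In 13.2, add adverse events so that the list matches 2.3.
2. In 13.3, state that AEs, ARs and SAEs are summarised by treatment actually received (OK432, BCG, none), with people selected for an agent but not dosed shown separately from controls. A table by randomised arm may be kept as supportive.

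The cost is about two sentences. No new data are needed, because section 12.4 already has adverse events collected at every visit from all participants, and administration is recorded on eCRFs (section 7.6). Intention to treat stays as it is for the efficacy outcomes.
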